**− Statistical analysis**

This will be done independently, both for randomized clinical trials and for cohort studies. In the case of clinical trials, the plan is to perform a statistical combination of the results of two or more individual studies identified through a meta-analysis, after screening for the presence of heterogeneity through the inconsistency test (I2), and the p value of the chi-square test, and if there is variation in the definition of the evaluated outcomes, statistical heterogeneity will be considered if an I2 greater than 40% or a p less than 0.10 is found in the chi-square test. The statistical combination of the results will be done through a meta-analysis of fixed effects or random effects if the data are heterogeneous. A sensitivity analysis will be carried out to study the influence of the risk of bias in the results of the meta-analysis. The presence of publication bias will be evaluated by means of a funnel plot and Egger's statistical test.

In the case of the cohort studies, the results of each outcome will be presented in the units of measurements reported in each study.

1. **Phase 2. Preliminary design of the contents of knowledge capsules in maternal and neonatal health**

Based on the results of the RSL, and following the methodologies described in the evidence for the development of the most effective KT strategies in health, the preliminary contents of the capsules will be designed, principally considering the key information for the preparation of the delivery and post-partum care which must be transmitted to pregnant women, which allows the generation of an adequate social transfer of knowledge. These contents will be defined in accordance with the domains described in the safe delivery checklist and will be designed for pregnant women who have a vaginal delivery as well as those who have a cesarean delivery.

These contents will be described independently, for the pre-partum, intra-partum and post-partum phase, and will include aspects related to patient safety, warning signs, interventions that will be received during delivery care and aftercare, both for normal delivery and for after surgery. It is proposed to make 2 capsules for each phase, one for each of the two possible means of delivery, for a total of 12 health capsules. The preliminary design of the 12 capsules will be carried out by the researchers of the group, and the proposal will be presented to the external experts in Phase 3.

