Based on the results of the systematic review of strategies for the transfer and social appropriation of knowledge, on the results of formal consensus of experts, and on the theoretical foundations of neurocognition and neuromarketing, the design of health knowledge capsules will be developed together with experts in health psychology, promotion and prevention in health, as well as experts in diagramming and development of audiovisual products. During this phase the final scripts, the graphic outline of the clips, their duration, the soundtrack and the production will be created, based on the results of the previous phases.

1. **Phase 5. Evaluation of effectiveness of knowledge capsules in terms of social appropriation of knowledge.**

A neuromarketing strategy will be applied in the Cognitive Neuroscience and Communication Laboratory of the National University of Colombia, with the objective of evaluating the effectiveness of the knowledge capsules in maternal and neonatal health in terms of social appropriation of knowledge, using measurements of attention, emotional response and remembrance.

The analysis will be conducted to find differences between subgroups or categories of educational level, defined as follows:

0 = No study

1 = Primary or Baccalaureate (basic education or secondary education)

2 = Higher Education (undergraduate and postgraduate)

*- Design:* Cross-over experimental study in which a group of pregnant women, non-pregnant women and adult men will be exposed to 13 clips, 12 of which will be produced through this knowledge transfer strategy and one will be an unrelated standard video that will be used as a control. The order of viewing the videos will be assigned randomly for each subject, so that each subject will have 13 evaluations. The random allocation tables will be generated by computer, and one will be made for each educational stratum (without education, with primary or secondary education, and with post-secondary education) and group (pregnant woman, non-pregnant woman and man). It is expected to have a minimum sample of 150 subjects.

*- Population and sample:*

- Inclusion criteria:

Pregnant women, non-pregnant women and men over 18 years of age, who agree to participate in the study through informed consent.

- Exclusion criteria:

participants who presented serious health problems linked to pregnancy or who presented any clinically significant visual and auditory problems, which affected the viewing of the videos.

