*- Type of sampling:* not probabilistic, for convenience.

*- Sample size:*

Using the statistical analysis program for biomedical, social and behavioral sciences G * Power 3, the sample size was calculated for a one-way analysis of variance (ANOVA) design and fixed effects, using the F statistic. The selection of the parameters was made for the recall outcome, expecting that the differences of the capsules compared with the video control would be moderate. The parameters were therefore defined as follows: moderate effect size f = 0.3; power (1-β) = 0.90 and alpha (α) = 0.05 for three groups. The calculation yielded a result of 144 for the total sample. Considering that there would be no follow-up of the participants and the measurements would be taken in a single session, a low number of losses was estimated (mainly due to failures in the registry), so a minimum of 150 subjects was defined as a total sample, 50 for each group.

*Process:*

All participants will sign an informed consent (Annex 1) after explaining the objectives of the study and procedures that will be carried out. Participation will be completely voluntary.

The procedure consists of the projection of 12 health knowledge capsules of approximately 35 seconds each, and a control clip, not related to the subject. The control clip will be a standard video, which provides information on reproductive health and maternal safety, but which has not been designed based on evidence or following strategies based on neuromarketing.

The observation of the videos will be free; that is, they will not be explained to the participants during the screening, or the content of them. All the videos will be seen by the participants, but the observation of each one will be assigned in a random way.

The successive order of visualization of the videos is presented in Figure 1. It shows the successive ordering of the clips. However, the actual order of visualization of the clips will be done randomly for each of the subjects.

[figure not shown]

***Figure 1.*** *Form in which the assignment and evaluation of the effect of each intervention is planned.*

The process of consolidating results will be done for each clip as shown in Figure 2.

***Figure 2.*** *Selected sample, and methodological format of analysis of the clips*

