During the screening of the health knowledge capsules, the eye tracking method will be applied to evaluate the attention of the subjects before the visual stimulus of the health capsules. By means of a Tobii TX 300 eye tracker and the Tobii Studio Software, the pupillary size in arbitrary units (AU), and the duration and direction of the fixation in seconds will be measured. Areas of interest will also be recorded, according to the stimuli in which the attention is fixed, the duration, and the order in which the visual exploration is performed.

The monitoring of the autonomous activity will be carried out through the registration of the electrodermal activity (Galvical Skin Reaction), which allows the evaluation the state or emotional reaction of the subjects. The record of electrodermal activity will be measured by the computerized psychophysiological recording equipment I-330-C2 + 12. (J & J Enterprises Seattle, WA). The measuring electrodes will be placed on the distal phalanx of the third and fourth finger of the non-dominant hand with SE-35 sensors connected to a T-601 preamplifier (J & J Enterprises Seattle, WA). For the analysis of results, the USE3 Software from Physiolab will be used (J & J Engineering, 2004).

The analysis of skin conductance data will be carried out with a procedure performed by Benedek and Kaernbach, through which the amplitude of the electrodermal response to a stimulus is obtained. Thus, two register values ​​will be recorded to calculate the amplitude: the conductance recorded in the lowest time of the latency period and the conductance peak. Subsequently, these values ​​and their registration will be subtracted. This analysis will be performed for each event identified in each capsule by each subject, to obtain an average of the conductance amplitudes for each grouping of images-events (positive, negative and neutral).

Between each video there will be a break of 5 to 10 seconds, and before starting the next video for evaluation there will be a neutral sequence in order to calibrate the response of the individual to a neutral state: this is considered to be the washout period between each video.

A parametrization of the measurements will be carried out in order to be able to relate both variables. Subsequently, a survey will be applied to evaluate the recall component.

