***Statistic analysis:***

Hypotheses raised:

- **Study hypothesis 1**

Comparison between capsules and video control

H0: μ capsule X = μ video control

Ha = μ capsule X ≠ μ video control

*μ = average attention, emotional reaction and recall*

- **Study hypothesis 2**

Comparison between groups: men, non-pregnant women, pregnant women

H0: μ1 = μ2 = μ3

Ha: ∃μj ≠ μ j = 1, 2, 3

*μ = average attention, emotional reaction and recall*

- **Study hypothesis 3**

Comparison between levels of schooling: none, primary, baccalaureate, undergraduate, postgraduate

H0: μ1 = μ2 = μ3

Ha: ∃μj ≠ μ j = 1, 2, 3, 4, 5

*μ = average attention, emotional reaction and recall*

- **Study hypothesis 4**

Comparison between family history: children, no children

H0: μ1 = μ2

Ha: μ1 ≠ μ2

*μ = average attention, emotional reaction and recall*

A descriptive analysis of the measured variables will be carried out. The qualitative variables will be described in proportions, and calculations for averages and standard deviation that follow a normal distribution will be performed for quantitative variables. For variables that do not follow this distribution, medians and interquartile ranges will be calculated. The normality of the variables will be evaluated by the Shapiro-Wilk test.

The difference between the averages of the variables of emotional reaction and attention will be carried out by means of an analysis of variance (ANOVA) for dependent samples, taking into account the effect of drag. For these comparisons, the non-parametric tests of Kruskal Wallis and the Wilcoxon rank sum will be used, according to the number of levels of each factor.

For the results of the survey, in which the recall of the contents of the capsules will be evaluated after their screening, an analysis will be made to compare the difference in proportions between the groups with a good level of recall and those with a low level of recall for each category of educational level.

Statistical software Stata 13.1 will be used to analyze the data.

1. **Phase 6. Final production of the health capsules in maternal and neonatal safety**

Professional experts in the layout and development of audiovisual animation products will carry out the final production process, taking into account the changes suggested by the analysis of results of the neuromarketing strategy.

- - - 1. **Ethical considerations**

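### As described, the recall survey does not support the capsule-versus-control comparison on recall in hypothesis 1

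*Protocol*

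**What the plan says.** All references are to the protocol, Phase 5 unless stated otherwise.

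- **Design.** A crossover with 12 capsules and one control video in random order, "so that each subject will have 13 evaluations".
- **Process, exposure.** "All the videos will be seen by the participants, but the observation of each one will be assigned in a random way". Everything takes place in a single session.
- **Process, gaps.** "Between each video there will be a break of 5 to 10 seconds", followed by a neutral sequence meant to bring the response back to a neutral state; "this is considered to be the washout period between each video".
- **Process, recall.** After the eye tracking, the skin conductance and the breaks have been described: "Subsequently, a survey will be applied to evaluate the recall component".
- **Statistic analysis, recall.** The survey is one "in which the recall of the contents of the capsules will be evaluated after their screening". The only recall analysis described compares good and low recall by educational level. Carry-over (translated as drag) is mentioned only in the sentence on emotional reaction and attention.
- **Hypothesis 1.** Capsule X against the control video, with recall among the three outcomes.
- **Sample size.** The parameters were set for recall, on the expectation of a moderate difference between the capsules and the control.
- **Phase 2, content.** "It is proposed to make 2 capsules for each phase, one for each of the two possible means of delivery".
- **Control clip.** Design and Process call it unrelated to the topic. Process then says that it informs about reproductive health and about safety of the mother.

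**The concern.** To test hypothesis 1 on recall, each subject needs a recall score for each capsule and one for the control, and each score must reflect what that clip taught. The protocol provides for neither. The survey is described for the capsules only, so the comparator may have no score at all. If the survey follows the screening, every respondent has already seen every clip, and the protocol does not require that an item be answerable from one clip alone.

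The washout does not fill the gap. Its stated purpose is a neutral response state, which suits skin conductance and pupil size. Learned content does not fade in a few seconds.

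Recall is one of the three effectiveness outcomes and the one used to size the study. Phase 6 revises the capsules in the light of the Phase 5 results. The timing of the survey, its items and the clips it covers must be settled before data collection, because no later analysis can recover them. They are therefore not details that a statistical analysis plan could supply afterwards.

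**Working it through.** **1. The plan's own figure.** Inputs from Sample size: one-way fixed-effects ANOVA, k = 3 groups, f = 0.3, alpha = 0.05, power 0.90. Power is the upper tail of a noncentral F with k − 1 and N − k degrees of freedom and noncentrality N × f². At N = 144 the noncentrality is 144 × 0.09 = 12.96 and the power is 0.9008, and 144 is the smallest N that reaches 0.90. At N = 150 the power is 0.913. The stated 144 reproduces, and nothing in this point changes it. It does confirm that recall, capsule against control, is the contrast that the protocol names when it justifies its size.

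**2. What hypothesis 1 needs, against what is described.**

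| Needed for recall under hypothesis 1 | Described in the protocol |
| --- | --- |
| A recall score for each capsule | A survey on the capsules; no score per clip |
| A recall score for the control | Not mentioned |
| Items that belong to one clip | Not mentioned |
| A capsule-versus-control analysis of recall | Only good versus low recall by educational level |
| Protection against carry-over of knowledge | A washout for physiological response; carry-over considered only for attention and emotional reaction |

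**3. Session timing.** Inputs from Process: about 35 s per capsule, 12 gaps of 5 to 10 s. The control is assumed to last 35 s too; the length of the neutral sequences is not given and is left out.

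- Viewing: 13 × 35 = 455 s.
- With breaks: 455 + 12 × 5 = 515 s, to 455 + 12 × 10 = 575 s.
- From the end of the first clip to the end of the last: 12 × 35 + 12 × 5 = 480 s, to 12 × 35 + 12 × 10 = 540 s.

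With one survey at the end, the delay runs from about zero for the last clip to 8–9 minutes for the first, plus the neutral sequences. Random order balances delay and position across clips on average. It does not alter total exposure: at the survey every subject has seen all 13 clips, whatever the order.

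**4. Why shared content matters.** Let a be the chance that clip A alone enables a correct answer, and b the same for clip B. If the content is in both, and the two act independently (a simplification), the chance of a correct answer is 1 − (1 − a)(1 − b). This is symmetric in a and b and the same in both viewing orders, so the survey cannot tell A from B. If the content is only in A, the chance is a, and the item measures A. What matters is whether items are specific to a clip, not simply that the survey comes last.

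**5. How much is shared.** The documents do not say. Overlap is plausible between the vaginal and caesarean capsules of the same phase, since Phase 2 lists safety, warning signs, interventions and aftercare for both. It is not established: the delivery-mode split is also a reason for contents to differ. The sentence quoted from Phase 2 gives 2 × 3 = 6 capsules rather than 12, so the pairing itself is unclear. Overlap with the control depends on which of its two descriptions holds.

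**6. If the survey followed each clip instead.** Knowledge from earlier clips would still be present for later ones. Only the first clip of a session would be free of it. With 150 subjects and all clips equally likely to come first, that is 150 / 13 ≈ 11.5 subjects per clip. Clip-specific items would be needed on this reading as well.

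**The case against.** The protocol never says outright that recall is surveyed once, after all 13 clips. It promises 13 evaluations per subject, says that results are consolidated for each clip, and refers to figures that are not available here. The neutral sequences have no stated length, so a short questionnaire between clips is not strictly ruled out. This stands: a single end-of-session survey is the natural reading, not a stated fact.

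A reader might go further and infer that recall can never be attributed to a clip, because everyone has seen everything. The documents do not support that. An end-of-session survey with clip-specific items would give a usable score per clip, and the random order already balances position and delay.

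A reader might also infer that capsule-versus-control differences are pulled towards zero. That does not follow either. If the control is off-topic, overlap among the capsules raises capsule recall and leaves control recall alone, which widens the contrast. If the control shares maternal content, its own score is raised and the contrast may shrink. Between capsules, unequal overlap can create differences as easily as hide them.

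Finally, the protocol makes no claim that the washout acts on memory. That is correct, and the criticism is only that nothing else in the plan deals with carry-over of knowledge. None of this supplies a control recall score, clip-specific items or a recall analysis for hypothesis 1.

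**Conclusion.** The point holds in this form: as described, the recall measurement does not support the recall part of hypothesis 1. Two gaps rest on the text directly. The survey is described for the capsules only, and no item is tied to a clip. Two further elements carry assumptions: that the survey comes once at the end (the natural reading), and that some clips share content (plausible, extent unknown).

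The size cannot be given as a number. If the control is not surveyed, the contrast has no comparator. If it is surveyed with unspecific items, the bias depends on an overlap that the protocol does not state, and its direction is open. The comparison by educational level does not need clip-level attribution, and the sample size figure stands as calculated. The protocol should be changed before Phase 5 begins.

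**What to change.** Keep the survey at the end of the session and specify it in the protocol as follows.

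1. State when it is given, and that it covers all 13 clips including the control.
2. Use the same number of scored items for each clip, each answerable from that clip only. Check this against the final scripts from Phase 4.
3. Report items on content shared by two or more clips for the set as a whole; do not count them in any clip's score.
4. For hypothesis 1, compare clip-level recall within subject, with viewing position (already randomised) in the comparison. The analysis by educational level can remain alongside.
5. State that the washout applies to skin conductance and eye tracking only.
6. Reconcile the Design and Process descriptions of whether the control is related to the topic.

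The cost is survey construction and protocol wording, with no added participants, visits or equipment. The downside is fewer usable items per clip where contents overlap.

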***Statistic analysis:***

Hypotheses raised:

- **Study hypothesis 1**

Comparison between capsules and video control

H0: μ capsule X = μ video control

Ha = μ capsule X ≠ μ video control

*μ = average attention, emotional reaction and recall*

- **Study hypothesis 2**

Comparison between groups: men, non-pregnant women, pregnant women

H0: μ1 = μ2 = μ3

Ha: ∃μj ≠ μ j = 1, 2, 3

*μ = average attention, emotional reaction and recall*

- **Study hypothesis 3**

Comparison between levels of schooling: none, primary, baccalaureate, undergraduate, postgraduate

H0: μ1 = μ2 = μ3

Ha: ∃μj ≠ μ j = 1, 2, 3, 4, 5

*μ = average attention, emotional reaction and recall*

- **Study hypothesis 4**

Comparison between family history: children, no children

H0: μ1 = μ2

Ha: μ1 ≠ μ2

*μ = average attention, emotional reaction and recall*

A descriptive analysis of the measured variables will be carried out. The qualitative variables will be described in proportions, and calculations for averages and standard deviation that follow a normal distribution will be performed for quantitative variables. For variables that do not follow this distribution, medians and interquartile ranges will be calculated. The normality of the variables will be evaluated by the Shapiro-Wilk test.

The difference between the averages of the variables of emotional reaction and attention will be carried out by means of an analysis of variance (ANOVA) for dependent samples, taking into account the effect of drag. For these comparisons, the non-parametric tests of Kruskal Wallis and the Wilcoxon rank sum will be used, according to the number of levels of each factor.

For the results of the survey, in which the recall of the contents of the capsules will be evaluated after their screening, an analysis will be made to compare the difference in proportions between the groups with a good level of recall and those with a low level of recall for each category of educational level.

Statistical software Stata 13.1 will be used to analyze the data.

1. **Phase 6. Final production of the health capsules in maternal and neonatal safety**

Professional experts in the layout and development of audiovisual animation products will carry out the final production process, taking into account the changes suggested by the analysis of results of the neuromarketing strategy.

- - - 1. **Ethical considerations**

The current project adheres to the ethical principles for medical research in human beings, promulgated by the Declaration of Helsinki of the World Medical Association [46] and in the resolution 008430 of 1993 of the Ministry of Health [47], which establishes the scientific, technical and administrative standards for health research. According to this resolution, this investigation is classified as having minimal risk, considering that it uses the data registry through standard procedures and the behavior of the subjects will not be manipulated. For this investigation, a signature of informed consent will be requested for the phases that require it. The entire project will be submitted for approval by an Ethics Committee.

1. **Confidentiality**

The information collected during the development of the project will be restricted to the research team; the information in digital media and databases will have access codes and the information in physical form will be stored on shelves under lock and key for 10 years.

1. **Expected results of the investigation**

After the research is completed, there will be 12 health capsules, designed using neuromarketing strategies, for the preparation of childbirth, both for vaginal delivery and cesarean delivery and the evaluation of their effectiveness in social appropriation of knowledge.

It is hoped that the research, through this strategy of KT, contributes to the knowledge of relevant and clear information for pregnant women and their families and to the empowerment of patients in maternal and neonatal health care. In the medium and long term it is expected that these capsules will be used to be disseminated in a variety of mass media and thus contribute to improve the knowledge and empowerment of the pregnant woman and her family, and in this way the intervention contributes to the improvement of the health and safety of these patients, with a lower proportion of obstetric complications related to pregnancy, childbirth and postpartum.

The project will contribute to the development of the lines of research in maternal and neonatal health and patient safety at the National University of Colombia and the Colombian Society of Anesthesiology and Resuscitation (S.C.A.R.E.).

Once the present work is completed, a second stage will be proposed in which the implementation of knowledge capsules in maternal and neonatal health will be carried out through mass media and the evaluation of their impact on maternal morbidity and mortality.

1. **Expected products**

Results of activities of Generation of New Knowledge

| **Product** | **Description** | **Number** | **Target result/product** |
| --- | --- | --- | --- |
| Knowledge transfer tool | Health capsules for preparing for childbirth, either natural or Cesarean. | 12 | General population, principally pregnant women  Health institutions, national scientific community, Equality in Health Group, Quality, Safety and Health Education Group, Neurosciences Group |
| Original article in national journal | Original article 1: Systemic literature review to evaluate the effectiveness of different KT health strategies. | 1 | Health institutions, national scientific community, Equality in Health Group, Quality, Safety and Health Education Group, Neurosciences Group |
| Original article in international journal | Original article 2: Evaluation of the effectiveness of social acceptance of maternal and neonatal through neuromarketing strategies. | 1 | Equality in Health Group, Quality, Safety and Health Education Group, Neurosciences Group |
| Master’s degree thesis | Evaluation of the effectiveness of social acceptance of maternal and neonatal through neuromarketing strategies. | 1 | Equality in Health Group, Quality, Safety and Health Education Group, Neurosciences Group |

Products results of activities of Strengthening the scientific community

| **Type of result** | **Expected result** | **Number** | **Beneficiaries** |
| --- | --- | --- | --- |
| Links with master’s degree student | Start training of a master’s degree student within the project framework | 1 | [name], with  CvLAC connection |
| Others | Educational tools for the patient to be applied by health personnel. | 12 | Health institutions, gyno-obstetric professionals |
| Others | Strengthening of the scientific capacities in the development of research projects. | 3 | Equality in Health Group, Quality, Safety and Health Education Group, Neurosciences Group |

Products results of Social Transfer of Knowledge

| **Product** | **Description** | **Number** | **Beneficiaries** |
| --- | --- | --- | --- |
| Scientific event | International congress | 1 | National scientific community, Equality in Health Group, Quality, Safety and Health Education Group, Neurosciences Group, National University |
| Scientific event | National congress | 1 | National scientific community, Equality in Health Group, Quality, Safety and Health Education Group, Neurosciences Group, National University |

1. **Studies of the research team**

S.C.A.R.E.'s studies in patient safety and its efforts in obstetrics has been directed through the research group "Quality, Safety and Health in Education" which, supported by the society's research area, has carried out multiple projects of research on safety in the area of ​​obstetrics, including "gynecology and occupational responsibility claims" carried out between 2004 and 2005, and "adverse events in gynecology" that in 2009 studied the patterns of conduct in medical practice in obstetrics to find out about these activities and generate measures of patient safety, and "Processes of care during pregnancy until the first week after delivery of women with identified risk factors attending the Rafael Calvo Maternity Clinic in the city of Cartagena" (2013). These investigations, as well as the rigorous revision of literature during recent years, have led to products such as the article "Obstetrics-Gynecology and the demands of professional responsibility in Colombia" published in the Medical-Legal Journal in 2005, the book chapters "New guidelines for Cardiopulmonary Resuscitation in pregnant women" published in the XIV Update Course in Gynecology and Obstetrics in 2006, and "Analgesia and anesthesia for the obstetric patient" published in 2004. Additionally, sustained work has been carried out on the checklists and their effectiveness which has resulted in the academic articles "The checklist: a standard of care" and "Verification of the checklist for safety in surgery from the patient's perspective" published in the Colombian Journal of Anesthesiology in 2013, the presentation "Safety in ambulatory surgical patients and experience of the checklist" presented at the National Congress of Anesthesiology in 2011, and the poster “Is the checklist justified as a strategy of the safety policy in the ambulatory surgical unit?”

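### Hypothesis 1 sets 12 capsule-versus-control comparisons on three co-equal outcomes, with no primary outcome and no control of type I error

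*Protocol*

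**What the plan says.** Under Design (Protocol, Phase 5), every subject is "exposed to 13 clips, 12 of which will be produced through this knowledge transfer strategy and one will be an unrelated standard video". The Phase 5 statistical analysis then states hypothesis 1, headed "Comparison between capsules and video control", capsule by capsule: "H0: μ capsule X = μ video control" against "Ha = μ capsule X ≠ μ video control". The mean in question is defined as "average attention, emotional reaction and recall", and the same definition is repeated under hypotheses 2 to 4. The three outcomes therefore have equal standing throughout.

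The methods that follow are a dependent-samples ANOVA or rank tests for attention and emotional reaction. For recall, the plan compares proportions with good and low recall within educational levels. The section names no primary outcome, no family of tests, no adjustment, and no rule for how many significant results would make a capsule effective.

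The only significance level given for Phase 5 stands in the sample size paragraph: "moderate effect size f = 0.3; power (1-β) = 0.90 and alpha (α) = 0.05 for three groups". That paragraph says its parameters were chosen for recall, in the expectation of moderate differences between capsules and control.

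**The concern.** Twelve capsules on three outcomes give 36 nulls, before hypotheses 2 to 4 are counted. All 12 contrasts on an outcome share one control mean, so a chance low or high control reading moves all of them together. With three co-equal outcomes and no stated family, any of the 36 results could be reported as the finding.

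Two things are at stake. One is the claim that the capsules are effective, which is the stated general aim and the subject of a planned article. The other is the set of changes carried into final production in Phase 6. A false finding that a capsule is worse than the control also matters there, because it could prompt a needless change.

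**Working it through.** **The plan's own figure.** The sample size paragraph says "the sample size was calculated for a one-way analysis of variance (ANOVA) design and fixed effects, using the F statistic". With k = 3, f = 0.3, α = 0.05 and N = 144, the noncentrality is λ = N·f² = 144 × 0.09 = 12.96 on (2, 141) degrees of freedom, and the power is 0.901. The stated 144 is reproduced; at N = 150 the power is 0.913. This is an F test between three independent groups. The 0.05 is therefore the level of that test; the protocol does not state it as the level of each capsule-control contrast.

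**Count of contrasts.** By the hypotheses, 12 capsules × 3 outcomes = 36. By the methods described, 12 × 2 = 24, because the recall analysis is by educational level and delivers no capsule-control contrast.

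**Independent tests at 0.05 (upper reference only).** 1 − 0.95^12 = 46.0%; 1 − 0.95^24 = 70.8%; 1 − 0.95^36 = 84.2%. Expected false positives in 36 tests: 36 × 0.05 = 1.8.

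**Shared control modelled.** Simulation of 200,000 runs with no true difference: 13 clip means per outcome, and contrasts z = (capsule − control)/√2, which have correlation 0.5 with each other. Significant means |z| > 1.96; in favour of a capsule means z > 1.96. The protocol gives no between-outcome correlation ρ, so a range is assumed.

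| ρ | Two outcomes, either direction | Three outcomes, either direction | Two outcomes, in favour | Three outcomes, in favour |
|---|---|---|---|---|
| 0 | 53.6% | 68.4% | 29.4% | 40.7% |
| 0.3 | 52.7% | 66.5% | 27.8% | 36.8% |
| 0.5 | 50.7% | 63.2% | 26.1% | 33.5% |
| 0.8 | 45.4% | 53.5% | 22.8% | 27.2% |
| 1 | 31.9% | 31.9% | 16.0% | 16.0% |

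For one outcome the figures are 32% in either direction and 16% in favour of a capsule.

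**If an omnibus ANOVA at 0.05 gated the contrasts for each outcome.** With no true difference anywhere, the chance over three outcomes is about 4–12% in either direction and 2–6% in favour of a capsule. The gate stops protecting once a capsule truly differs by enough to open it. The other 11 contrasts, still tested at 0.05 against the shared control, then carry a 30% chance of at least one false difference per outcome (simulated 30.3%).

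**The case against.** The strongest reply has four parts.

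- **The described analysis is an ANOVA, not 36 separate tests.** This is partly right. The methods yield about 24 capsule-control contrasts, and a gating ANOVA would bring the error down to 4–12% if no capsule differs. But the protocol does not say that the ANOVA gates anything. The sponsor also expects moderate differences, which is the situation in which a gate no longer helps.
- **Adjustment is often left to a statistical analysis plan.** True, and one may exist. However, this protocol contains a full analysis section with hypotheses, tests and software. That section gives three outcomes equal rank while the sizing rests on recall alone. The mismatch is within the document and should be resolved there.
- **It is a pilot, and all 12 capsules are to be produced whatever the tests show.** This limits the harm: no rule selects or drops a capsule on a p-value. It does not remove the stated aim of evaluating effectiveness, or the use of the results to change the capsules.
- **The size can be overstated.** A reader might infer that at least one capsule will more likely than not be declared effective by chance. The calculations do not support that. The figures above one half count differences in either direction. A false result in favour of a capsule has a chance of 16–41% and reaches 60% (1 − 0.975^36) only if all 36 tests are independent, which a shared control rules out. Nor does the protocol say that each contrast will be tested at 0.05; that is the natural reading, but an assumption.

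**Conclusion.** The point holds as a gap in the stated hypotheses. There are up to 36 capsule-control comparisons (about 24 under the methods described), on three co-equal outcomes, with no primary outcome and no control of type I error.

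If they are tested unadjusted, even the most favourable case, one outcome, gives a 32% chance of a false difference, more than six times the nominal 5%. Two outcomes, which is what the methods now deliver, give 45–54%. All three give 53–68%. The directional risk, a capsule falsely shown better than the control, is about 16–41% and stays below one half in every case with the shared control.

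These figures assume no true difference for any capsule, testing at 0.05, large-sample contrasts, and between-outcome correlations of 0 to 0.8 for the two- and three-outcome ranges (the directional range runs up to correlation 1). The correlations are assumptions, since the protocol gives none. The defect can be put right in the text and does not call the design or the sample size of 150 into question.

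**What to change.** Amend the Phase 5 statistical analysis as follows.

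1. Name recall as the primary outcome for hypothesis 1, in line with the sample size paragraph.
2. Reconcile the recall analysis with hypothesis 1, so that it compares each capsule with the control within subject. The comparison by educational level can stay as a separate analysis.
3. Test the 12 contrasts with Holm or a Dunnett-type adjustment at an overall two-sided 0.05, and state that level for the analysis.
4. Treat attention and emotional reaction as secondary, each adjusted over its own 12 contrasts, and hypotheses 2 to 4 as exploratory.

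**Cost.** This is about one paragraph and needs no extra subjects. For a paired mean contrast with N = 150 and 90% power, the detectable difference in SDs of the difference is about (z₁₋α/₂ + 1.282)/√150. Unadjusted it is (1.960 + 1.282)/12.247 = 0.265, or 0.27 with the t distribution. At the Bonferroni level 0.05/12 = 0.00417 it is (2.865 + 1.282)/12.247 = 0.339, or 0.34 with the t distribution. Holm and Dunnett-type methods lose no more than this, so 0.34 is the ceiling. If recall is kept as a good/low classification, the loss has to be worked out separately for paired proportions, because the protocol gives no expected proportions.
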